### Study endpoints

The primary endpoint is the effect of oral vitamin D at 5,000 and 10,000 IU/day compared with placebo on the frequency of CD4 T-cell subsets and cytokine responses in peripheral blood mononuclear cells in patients with CIS and in healthy control participants at weeks 16 and 24 compared with baseline.

Secondary endpoints include: the following. 1) In the patients with CIS having MRI brain scans at baseline and week 24, the number of new and enlarging T2 lesions and gadolinium-enhancing lesions at week 24 compared with baseline in patients receiving oral vitamin D at 5000 IU and 10,000 IU/ day compared with placebo, 2) In the patients with CIS, the effects of oral vitamin D at 5,000 and 10,000 IU/day compared with placebo on relapse occurrence, calculated as the annualized relapse rate (ARR), the percentage of patients who are relapse-free, and time to first relapse. 3) The effects of oral vitamin D at 5,000 and 10,000 IU/day compared with placebo on the percentage of treated patients with CIS who are free from any evidence of disease (clinical and MRI) activity.

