### Sample size

The power calculations for this study were based on a pilot study, which examined immunologic outcomes in four healthy control participants treated with vitamin D 5,000 to 10,000 IU/day at our institution [32]. All calculations for numbers needed in the study were based on α = 5% and β = 80%. Based on flow cytometry analysis of T-cell subsets, the change in IL-17-producing CD4 T-cells (Th17 cells) had an effect size (mean ± SD) of 1.9 ± 1.8 indicating a need for five study subjects per group for 80% power. For IFN-γ-producing CD4 T-cells (Th1 cells), the effect size was 4.3 ± 6.3) indicating a need for 19 subjects per group for 80% power. The changes noted in cytokines in response to anti-CD3 stimulation of PBMC were 1) for IL-17, Δ = 44.5 ± 44.3, thus 10 participants needed in each group; 2) for IFN-γ, Δ = 32.8 ± 1.2, thus 6 needed in each group; and 3) for IL-10, Δ = −455 ± 27, thus number needed is < 5. The changes noted in cytokines in response to PPD stimulation were 1) for IFN-γ, Δ = 1860 ± 1835, thus 10 needed, in each group and 2) for IL-10, Δ = −576 ± 86, thus number needed is <5. On the basis of these results, at least 10 subjects should be included in each group (the only immunologic endpoint not powered would be the flow cytometry analysis of the IFN-γ-producing cells). Recruiting 39 healthy controls and 45 patients with CIS will allow for a drop-out rate of 20% and 30% respectively.

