### Statistical methods

All analyses assume a two-sided test of hypothesis with an overall α level of 0.05. Immunologic endpoints and *post hoc* analyses, which will include the 16 and 24 week endpoints, are considered exploratory, and will not be adjusted for multiple comparisons. Descriptive statistics will be presented as mean ± SD. Non-parametric tests will be used to compare characteristics between treatment groups. For outcomes, the sign/sign rank test will be used to evaluate continuous outcomes. McNemar testing will be used to categorize categorical and binary outcomes. For non-parametric testing on unpaired continuous data, the Wilcoxon rank sum test will be used. All outcomes will be adjusted for baseline serum 25(OH)D levels, and for mean serum levels achieved at weeks 16 and 24.

Missing data will be imputed as the mean of the preceding and following measurements. Only patients completing at least 4 months of full participation in the study or experiencing a relapse at any time in the study will be included in the final analysis. Non-adherent participants, defined as those with an increase in serum level of 25(OH)D of less than 50 nmol/l from baseline, will be excluded from the final analysis.

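### The sample size reproduces as a before-after calculation in treated people only, so the stated 80% power does not carry over to the dose-versus-placebo comparison for the endpoints that set n = 10

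*Protocol article*

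**What the plan says.** The Sample size section of the protocol article says the calculations were "based on a pilot study, which examined immunologic outcomes in four healthy control participants treated with vitamin D 5,000 to 10,000 IU/day". It reports a mean change and SD for seven immunologic measures and converts each into a number per group for 80% power at α = 5% (the text calls the 80% β, evidently meaning power). Two of the seven set the size: "for IL-17, Δ = 44.5 ± 44.3, thus 10 participants needed in each group" and "for IFN-γ, Δ = 1860 ± 1835, thus 10 needed, in each group". The section concludes "On the basis of these results, at least 10 subjects should be included in each group" and adds in parentheses that IFN-γ-producing CD4 cells (Th1) by flow cytometry would be the one immunologic endpoint without adequate power. Recruitment of 39 controls and 45 patients then allows for 20% and 30% drop-out.

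Under Study endpoints: "The primary endpoint is the effect of oral vitamin D at 5,000 and 10,000 IU/day compared with placebo", measured as change from baseline. Randomization is to three equal arms within each population.

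Under Statistical methods: "All analyses assume a two-sided test of hypothesis with an overall α level of 0.05". Continuous outcomes are to be evaluated with sign or signed rank tests, and "For non-parametric testing on unpaired continuous data, the Wilcoxon rank sum test will be used".

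The Discussion describes the trial as having adequate power for its primary endpoint.

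**The concern.** The pilot inputs describe change in people who all took vitamin D. The section reports no placebo change and no placebo SD. A size derived from these inputs alone answers whether one arm's own change differs from zero. The primary endpoint asks whether the change on a dose differs from the change on placebo in other people. That contrast carries the sampling error of both arms and so needs more participants for the same effect.

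What is at stake is how the results are read. The article tells readers that every immunologic endpoint except Th1 has 80% power at 10 per group. If the power for the placebo comparison is materially lower, a non-significant result on IL-17, IFN-γ after PPD or Th17 is much weaker evidence of no effect than those statements imply.

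**Working it through.** **Inputs** (Sample size section), as mean change divided by SD:

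- IL-17, anti-CD3: 44.5 / 44.3 = 1.005; stated n 10
- IFN-γ, PPD: 1860 / 1835 = 1.014; stated n 10
- Th1 cells: 4.3 / 6.3 = 0.683; stated n 19
- Th17 cells: 1.9 / 1.8 = 1.056; stated n 5
- IFN-γ, anti-CD3: 32.8 / 1.2 = 27.3; stated n 6
- IL-10, anti-CD3: 455 / 27 = 16.9; stated n below 5
- IL-10, PPD: 576 / 86 = 6.7; stated n below 5

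All calculations are two-sided at 5%, with power from the noncentral t distribution.

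**Step 1: reproduce the stated sizes.** For a one-sample (before-after) t-test, the noncentrality is d√n with n − 1 degrees of freedom.

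- IL-17: n = 10 gives 1.005 × √10 = 3.18 against a critical value of 2.26, power 80.7%; n = 9 gives 75.2%. Required: 10.
- IFN-γ/PPD: n = 10 gives 81.3%; n = 9 gives 75.9%. Required: 10.
- Th1: n = 19 gives 80.3%; n = 18 gives 77.9%. Required: 19.

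All three match. Two-sample tests on the same inputs do not: two-sided z gives 16, 16 and 34; two-sided t gives 17, 17 and 35; one-sided versions give 13, 13 and 27 or 28. The drop-out step is sound: 10 / 0.8 = 12.5, rounded up to 13, and 10 / 0.7 = 14.3, rounded up to 15.

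Two stated sizes do not follow from the one-sample t-test: Th17 (stated 5, computed 10) and IFN-γ/anti-CD3 (stated 6, computed 2). Neither sets the chosen n.

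**Step 2: the comparison in the primary endpoint.** For two independent arms of n each, the noncentrality is d√(n/2) with 2n − 2 degrees of freedom. This assumes that the pilot change is the true drug effect, that the mean placebo change is zero and that both arms have the same SD. At n = 10 the IL-17 value is 1.005 × √5 = 2.25 against a critical value of 2.10.

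| Endpoint | Power, 10 per arm | n per arm for 80% |
|---|---|---|
| IL-17, anti-CD3 | 56.6% | 17 |
| IFN-γ, PPD | 57.3% | 17 |
| Th17 | 60.8% | 16 |
| Th1 (already conceded) | 30.3% | 35 |
| IFN-γ, anti-CD3; IL-10, both stimuli | near 100% | below 5 |

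By rank sum test (simulation, normal data), IL-17 power at 10 per arm is about 51% to 52%.

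With no drop-out at all, IL-17 power is 69% at 13 per arm and 76% at 15.

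The standardized difference with 80% power at 10 per arm is 1.325 SD: 1.325 × 44.3 = 58.7 for IL-17 (assumed 44.5), and 1.325 × 1835 = about 2,430 for IFN-γ/PPD (assumed 1,860).

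**Step 3: range over the unknown placebo SD.** IL-17, zero mean change on placebo, by simulation:

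| Placebo SD / treated SD | Pooled t, 10 per arm | Welch, 10 per arm | Welch, 13 per arm | Welch, 15 per arm |
|---|---|---|---|---|
| 1 | 57% | 56% | 69% | 76% |
| 0.75 | 67% | 66% | 79% | 85% |
| 0.5 | 77% | 75% | 86% | 91% |
| 0.25 | 83% | 79% to 80% | 90% | 94% |

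**The case against.** Five points can be made for the plan.

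*The test is not named.* The before-after method is inferred, and two of the five exact sizes do not fit it. That stands as a caution. But the two sizes that fix n = 10, and the Th1 size, match to the unit, and none of the two-sample versions tried gives that set.

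*Signed rank tests are planned for continuous outcomes.* A within-arm signed rank test at n = 10 has about 79% power for IL-17, so the sizing roughly suits such an analysis. But a within-arm test does not answer a placebo-controlled question. The same sentence does mean that the rank sum test should not be treated as the settled primary analysis. It is named only for unpaired data, and the outcomes are also to be adjusted for 25(OH)D. The 51% to 52% is therefore a side figure.

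*The placebo SD is unknown.* This stands, and it limits the size of the finding. The treated SD may include variation in drug response and in dose, so a smaller placebo SD is possible. A reader might infer that neither population can reach 80% even without drop-out. The article does not support that: at a placebo SD of 0.75 of the treated SD, power is about 79% at 13 per arm and 85% at 15. The mean placebo change is unknown too. A change in the same direction as on vitamin D lowers power; one of 0.25 SD in the opposite direction raises it to about 76% at 10 per arm.

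*An SD from four people is imprecise.* Under normality its 95% interval runs from 0.57 to 3.7 times the estimate. With the mean held fixed and equal SDs, power at 10 per arm then runs from about 96% to below 10%. This argues for a range in the text, not for keeping 80%.

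*The trial is exploratory.* The article uses that label to justify not adjusting for multiple comparisons. It does not make a stated power correct, and the Discussion still claims adequate power.

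**Conclusion.** The point holds for the endpoints that set the size. The calculation omits the placebo arm's sampling error, so 10 per arm does not give 80% power for the primary comparison on IL-17/anti-CD3 or IFN-γ/PPD, unless placebo responses vary far less than treated ones. Power is about 57% under equal SDs and zero mean placebo change. At 10 per arm it reaches about 80% only when the placebo SD is near a quarter of the treated SD, for which the article offers no evidence. Th17 also falls short, at about 61% under equal SDs, so Th1 is not the only endpoint affected.

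A reader might infer that the trial as a whole has 57% power. It does not follow: the figure belongs to two of seven endpoints, and three others keep near-100% power on their stated SDs. Nor does it follow that the trial must be enlarged. What is wrong is the stated power, which an exploratory trial can correct without changing its size.

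**What to change.** In the Sample size section, redo the calculation for change on each dose against change on placebo in two independent arms, and name the test. State the assumptions on placebo SD and mean placebo change. Report the difference detectable with 80% power at 10 evaluable per arm (about 1.33 SD with equal SDs), and power per endpoint with a range over the placebo SD, rather than one figure. Note that 80% for the two size-setting endpoints would take 17 per arm with equal SDs. Recheck the Th17 and IFN-γ/anti-CD3 sizes in the same pass.

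Correct the parenthesis that names Th1 as the only endpoint without adequate power, and qualify the claim of adequate power in the Discussion. In Statistical methods, say which test carries the comparison with placebo, so that sizing, endpoint and analysis refer to the same contrast.

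The cost is a rewritten paragraph, a few sentences elsewhere and a less favourable stated power. Recruitment is unchanged.

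### The recruitment margin covers drop-out only, but the plan also excludes non-adherent participants, so 10 evaluable per arm is not assured

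*Protocol article*

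**What the plan says.** The Sample size section of the protocol article takes several immunologic measures from a four-person pilot, derives a number needed for each, and concludes: "On the basis of these results, at least 10 subjects should be included in each group". Two measures set that number. For anti-CD3 stimulation the text reads "for IL-17, Δ = 44.5 ± 44.3, thus 10 participants needed in each group", and for PPD stimulation "for IFN-γ, Δ = 1860 ± 1835, thus 10 needed, in each group". The section ends: "Recruiting 39 healthy controls and 45 patients with CIS will allow for a drop-out rate of 20% and 30% respectively". The Randomization section provides for equal arms within each population, so the totals mean 13 per arm in controls and 15 per arm in CIS.

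The Statistical methods section then fixes who enters the final analysis, through two separate rules. One admits patients with at least four months of full participation, or with a relapse at any time. The other reads: "Non-adherent participants, defined as those with an increase in serum level of 25(OH)D of less than 50 nmol/l from baseline, will be excluded". No expected frequency of non-adherence is given, and neither section links this exclusion to the drop-out allowance.

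**The concern.** The margin above 10 per arm was sized for one kind of loss, people leaving the trial. The adherence rule removes people who stayed, attended and gave samples. If both losses come out of the same 13 or 15, the number analysed can fall below the minimum on which the sample size rests. The Discussion describes the trial as adequately powered for its primary endpoint, and that description depends on 10 evaluable participants in each group.

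**Working it through.** **Inputs.** Minimum of 10 per group, totals of 39 and 45, and drop-out of 20% and 30% (Sample size). Equal allocation to three arms (Randomization). Exclusion for a 25(OH)D rise below 50 nmol/l, and two-sided testing at 0.05 (Statistical methods). Target power of 80% (Sample size, where it is printed as β). The non-adherence rate q among those retained is not in the document, so 5%, 10% and 20% are assumed.

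**Step 1: reproduce the totals.** Number per arm = 10 / (1 − drop-out), rounded up.
- Controls: 10 / 0.8 = 12.5, so 13 per arm and 39 in all.
- CIS: 10 / 0.7 = 14.3, so 15 per arm and 45 in all.

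Both totals reproduce exactly.

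**Step 2: what drop-out leaves.**
- Controls: 13 × 0.8 = 10.4.
- CIS: 15 × 0.7 = 10.5.

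**Step 3: room for any further exclusion.**
- Controls: 1 − 10 / 10.4 = 3.8%, or 0.4 of a person per arm.
- CIS: 1 − 10 / 10.5 = 4.8%, or 0.5 of a person per arm.

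At the full planned drop-out, one exclusion takes the expected count to 9.4 or 9.5.

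**Step 4: effect of an assumed q in an active arm.** Expected evaluable = arm × (1 − drop-out) × (1 − q). The chance of keeping 10 or more is the upper tail of a binomial with 13 or 15 trials and success probability (1 − drop-out)(1 − q), with losses treated as independent.

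| q | Controls: expected | Controls: chance of ≥ 10 | CIS: expected | CIS: chance of ≥ 10 |
|---|---|---|---|---|
| 0% | 10.4 | 0.75 | 10.5 | 0.72 |
| 5% | 9.9 | 0.62 | 10.0 | 0.61 |
| 10% | 9.4 | 0.49 | 9.5 | 0.50 |
| 20% | 8.3 | 0.25 | 8.4 | 0.29 |

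**Step 5: what a shortfall does to power.** The Sample size section names no test. A two-sided within-arm paired t-test needs 10 for both endpoints that set the minimum (44.5 / 44.3 = 1.005 and 1860 / 1835 = 1.014), so it is a plausible reconstruction. At a standardised change of 1 its power is 0.803 with 10, 0.748 with 9 and 0.681 with 8. With the IL-17 figures themselves it is 0.807, 0.752 and 0.685.

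**The case against.** The drop-out inflation is arithmetically right, and nothing here says otherwise. The rest of the case for the plan is about how much follows.

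- **A tolerance is not a forecast.** The section says what drop-out the totals can absorb, not that all of it will happen. If drop-out were half the allowance (an assumption), 10% non-adherence would leave 13 × 0.9 × 0.9 = 10.5 and 15 × 0.85 × 0.9 = 11.5 per active arm. This stands.
- **Some who leave still count.** The completion rule keeps patients who leave after four months and those who relapse, so not every drop-out is lost to the analysis. This stands and softens the loss somewhat.
- **Drop-out may have been meant to cover all losses.** Possible in a condensed article, but the text does not say so and gives non-adherence its own rule. If that was the intention, it needs stating.
- **The power figures rest on a test the plan does not name.** Correct. The Statistical methods section lists sign, signed-rank and rank-sum tests, while the primary endpoint is a comparison with placebo. The figures in Step 5 describe change within one arm only.
- **The trial is exploratory and the pilot had four participants.** The step from 80% to 75% power is small beside the uncertainty in those standard deviations. This limits the consequence but does not reconcile the two sections.

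A reader might infer that the plan fails to deliver 10 per arm, or that active arms will usually fall short. The document does not support either. It gives no non-adherence rate. Even with the whole drop-out allowance used, an active arm keeps 10 or more with probability about 0.61 to 0.62 at 5% non-adherence, and about one half at 10%.

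The exclusion is also not worded as limited to the vitamin D arms. Its literal application to placebo is a separate problem, and the figures here do not rely on it.

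**Conclusion.** The two sections do not fit together. The allowance covers drop-out alone, and the analysis rules then remove a further group for which almost nothing was set aside. The minimum of 10 evaluable per arm is therefore not assured. That missing allowance follows from the document's own figures. The size of any shortfall does not: it depends on an assumed non-adherence rate and on drop-out reaching the full 20% and 30%. Over the assumed range of 5% to 20%, the expected shortfall in an active arm runs from essentially none to about 1.7 participants. On the reconstructed within-arm test, 8 or 9 evaluable participants would mean power of about 68% or 75% rather than 80%. This is a mismatch worth correcting, not an error in the recruitment totals.

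**What to change.** Keep 39 and 45, and do one of the following.

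1. **Preferred.** Do not exclude participants from the main analysis for a small 25(OH)D rise, and report the adherent subset as a sensitivity analysis. Only drop-out then draws on the allowance, and a post-randomisation exclusion that could bias the comparison goes. The cost is possible dilution of the effect in the main analysis.
2. **Otherwise.** Restate the allowance as loss from the final analysis for any reason, including under four months' participation and non-adherence: at most 3 of 13 (23%) in each control arm and 5 of 15 (33%) in each CIS arm. Give the power at 8, 9 and 10 evaluable per arm, and name the test and comparison it refers to. The cost is a slightly less favourable stated allowance and power.

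Either change takes a sentence or two in the Sample size or Statistical methods section and needs no added recruitment.

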### Statistical methods

All analyses assume a two-sided test of hypothesis with an overall α level of 0.05. Immunologic endpoints and *post hoc* analyses, which will include the 16 and 24 week endpoints, are considered exploratory, and will not be adjusted for multiple comparisons. Descriptive statistics will be presented as mean ± SD. Non-parametric tests will be used to compare characteristics between treatment groups. For outcomes, the sign/sign rank test will be used to evaluate continuous outcomes. McNemar testing will be used to categorize categorical and binary outcomes. For non-parametric testing on unpaired continuous data, the Wilcoxon rank sum test will be used. All outcomes will be adjusted for baseline serum 25(OH)D levels, and for mean serum levels achieved at weeks 16 and 24.

Missing data will be imputed as the mean of the preceding and following measurements. Only patients completing at least 4 months of full participation in the study or experiencing a relapse at any time in the study will be included in the final analysis. Non-adherent participants, defined as those with an increase in serum level of 25(OH)D of less than 50 nmol/l from baseline, will be excluded from the final analysis.

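### Paired tests are assigned to outcomes defined as dose versus placebo in parallel arms: McNemar is invalid for the binary endpoints, rank-sum is not tied to the placebo contrast, and no named test carries the 25(OH)D adjustment

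*Protocol article*

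**What the plan says.** The Study endpoints section frames the primary immunologic endpoint and the MRI, relapse and disease-activity endpoints in patients with clinically isolated syndrome (CIS) as each dose against placebo. One binary endpoint is "the percentage of treated patients with CIS who are free from any evidence of disease (clinical and MRI) activity"; another is the percentage relapse-free. The immunologic endpoint is also described as a change from baseline to weeks 16 and 24. The Randomization section allocates different people to three arms, separately in patients and in healthy controls.

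The Statistical methods section then names its tests: "For outcomes, the sign/sign rank test will be used to evaluate continuous outcomes. McNemar testing will be used to categorize categorical and binary outcomes". The next sentence gives the Wilcoxon rank sum test for unpaired continuous data without linking it to an endpoint. The sentence after that begins "All outcomes will be adjusted for baseline serum 25(OH)D levels" and goes on to require adjustment for the levels achieved at weeks 16 and 24. An earlier sentence uses non-parametric tests to compare characteristics, not outcomes, between treatment groups. No unpaired test for binary outcomes and no regression model is named.

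**The concern.** A signed-rank test asks whether one arm changed over time. McNemar asks whether a binary status changed in the same, or matched, people. Neither asks whether a dose differs from placebo, which is the question the trial was randomized to answer.

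A within-arm change also contains anything that moves all arms together, such as season or recovery after the acute event (patients with CIS enter within 3 months of symptom onset). If such changes were reported as effects of vitamin D, the placebo arm would serve no purpose. The sample size section suggests that this is more than loose wording, because its figures come from a within-group calculation.

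**Working it through.** **1. Do the named tests fit the endpoints?**

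| Endpoint | Test named | Fit |
|---|---|---|
| Immune measures, dose vs placebo | Sign/signed-rank; rank-sum for unpaired continuous data in general | Paired test does not address the contrast; rank-sum on change scores would, but is not assigned to it |
| Relapse-free, disease-activity-free | McNemar only | Invalid: status over 24 weeks has no baseline counterpart, and patients are not matched across arms |
| Any outcome, adjusted for 25(OH)D | All of the above | None takes a covariate |

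If new-lesion counts are treated as continuous outcomes, they cannot be negative. A sign test against zero is then significant in any arm where six patients have a new lesion (2 × 0.5^6 = 0.031), placebo included.

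**2. The plan's own sample sizes.** Inputs from the Sample size section: "All calculations for numbers needed in the study were based on α = 5% and β = 80"% (80% is evidently the power), and a pilot "which examined immunologic outcomes in four healthy control participants treated with vitamin D 5,000 to 10,000 IU/day", with no placebo group mentioned. With d = mean change / SD and two-sided α = 0.05:

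| Measure | d | Stated n | Paired t | Two-sample t, per arm | Two-sample power at 10 per arm |
|---|---|---|---|---|---|
| Th1 | 4.3/6.3 = 0.683 | 19 | 19 | 35 | 30% |
| IL-17, anti-CD3 | 44.5/44.3 = 1.005 | 10 | 10 | 17 | 57% |
| IFN-γ, PPD | 1860/1835 = 1.014 | 10 | 10 | 17 | 57% |
| Th17 | 1.9/1.8 = 1.056 | 5 | 10 | 16 | 61% |

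The stated 19, 10 and 10 are reproduced by the two-sided paired one-sample t calculation and by no two-sample variant tried. The stated 5 for Th17 is not reproduced (the paired z one-sided version gives 6), nor is the stated 6 for anti-CD3 IFN-γ (d = 32.8/1.2 = 27, n about 2). The recruitment totals do follow from 10 per group: 10/0.8 = 12.5, so 13, × 3 = 39; 10/0.7 = 14.3, so 15, × 3 = 45. The two-sample columns assume no mean change on placebo and the pilot SD in both arms.

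**3. What if within-arm results were read as treatment effects?** Assume no drug effect, 10 completers per arm and a shared change of δ SD in every arm. Let p be the power of the within-arm test at δ. The probability of dose significant and placebo not is p(1 − p) for one dose and [1 − (1 − p)²](1 − p) for either dose.

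| δ (SD, assumed) | p | One dose | Either dose |
|---|---|---|---|
| 0 | 0.050 | 4.8% | 9.3% |
| 0.25 | 0.109 | 9.7% | 18.4% |
| 0.5 | 0.293 | 20.7% | 35.4% |
| 0.63 | 0.429 | 24.5% | 38.5% |
| 0.7 | 0.506 | 25.0% | 37.3% |
| 1.0 | 0.803 | 15.8% | 18.9% |

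Simulation with the signed-rank test agrees: 21% for one dose at 0.5 SD and 17% at 1 SD; for either dose about 34% at 0.5 SD and 38% at 0.65 SD. Between-arm rank-sum tests on the same data reject in 4% to 5% of trials per dose. For either dose against the shared placebo, unadjusted, they reject in about 8%, whatever the shared change.

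**The case against.** The strongest reply is that a between-arm test for continuous data is named. The primary endpoint has a paired element (against baseline) and an unpaired one (against placebo), so signed-rank for the first and rank-sum on change scores for the second is a coherent reading. This stands. A reader might infer that the plan has no valid test of dose against placebo for continuous outcomes, and the text does not support that. What remains is that the sentence about outcomes assigns the paired test and the rank-sum sentence is linked to no endpoint. Rank-sum also helps neither the binary endpoints nor the adjustment.

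Second, the plan nowhere says that a dose will be declared effective because it reaches significance and placebo does not. This stands too. The error rates above are conditional on that misreading and on a shared change the documents do not give. The fair comparator for either dose is about 8%, not 5%, since the plan openly declines multiplicity adjustment for the immunologic endpoints.

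Third, assay drift is a weak source of shared change, because cells are frozen until all three time points are collected. Season and the clinical course are more plausible.

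Fourth, this is a condensed article, and the choice of model, the handling of counts and the test for time to relapse may sit in an analysis plan. Silence on those is no fault. But the article does name tests, and those it names conflict with its endpoints and with its adjustment rule. The exploratory label relaxes multiplicity control; it does not remove the placebo contrast.

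**Conclusion.** Wrong as written for the binary endpoints, where McNemar is the only test named and cannot be applied to independent arms. Wrong as written also for the adjustment, which no named test can carry. For continuous endpoints the text is ambiguous: a valid between-arm test is mentioned but not assigned to the placebo comparison.

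A reader might infer a false-positive rate of more than a third for this trial. The documents do not support that as a property of the plan. It would arise only if within-arm significance were compared informally and the shared change were near 0.5 to 0.75 SD. Over 0 to 1 SD the range is about 5% to 25% per dose and 9% to 38% for either dose, with 10 per arm, normal changes and no drug effect.

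The sizing is also within-group. For the between-arm question, 10 per arm gives about 57% power for anti-CD3 IL-17 and PPD IFN-γ, if placebo shows no mean change and the pilot SD holds.

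**What to change.** State in the Statistical methods section that each dose is compared with placebo, separately in patients and in healthy controls, by a between-arm method:

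- **Continuous immune endpoints:** a model of the week-16 and week-24 values (ANCOVA, on a log or rank scale if skewed), adjusted for the same measure at baseline and for baseline 25(OH)D, giving the difference and 95% confidence interval. If unadjusted, use rank-sum on change from baseline.
- **Relapse-free and disease-activity-free:** Fisher's exact test or exact logistic regression in place of McNemar.
- **Lesion counts:** a between-arm rank-sum test or a count model.
- **Signed-rank tests:** within-arm description only.

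This proposal deliberately leaves achieved 25(OH)D out of the main comparison. It is measured after randomization and driven by treatment, so adjusting for it would remove part of the effect. It can be examined in a separate exploratory analysis.

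The analysis change is rewording, with standard software and no new data, and should be made before the database is locked. The real cost is that the power statement must be restated for the between-arm comparison. On the same assumptions, IL-17 power is about 69% with 13 per arm and 76% with 15 per arm if nobody drops out. Reaching 80% takes 17 completers per arm: 17/0.8 = 21.3, so 22 × 3 = 66 controls, and 17/0.7 = 24.3, so 25 × 3 = 75 patients. If recruitment is not enlarged, the Discussion's claim of adequate power for the primary endpoint should be revised.

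### The target of 10 per group is a size for within-person change, but the primary endpoint compares each dose with placebo, where 10 per group gives roughly 51–52% power by the planned rank sum test, not 80%

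*Protocol article*

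**What the plan says.** All references are to the Protocol article.

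- **Study endpoints** defines the primary endpoint as the effect of 5,000 and 10,000 IU/day compared with placebo on T-cell subsets and cytokine responses, at weeks 16 and 24 relative to baseline, in patients and in healthy controls.
- **Sample size** takes its effects from "a pilot study, which examined immunologic outcomes in four healthy control participants treated with vitamin D 5,000 to 10,000 IU/day" and mentions no placebo group in that pilot. The error rates are given as "All calculations for numbers needed in the study were based on α = 5% and β = 80" percent, where the 80 can only be the power. Each endpoint has a mean ± SD change and a number per group, but no test is named. Some numbers are very small: Th17 cells "had an effect size (mean ± SD) of 1.9 ± 1.8 indicating a need for five study subjects per group for 80% power", and for IL-10 "thus number needed is < 5". The section concludes: "On the basis of these results, at least 10 subjects should be included in each group".
- **Statistical methods** states "All analyses assume a two-sided test of hypothesis with an overall α level of 0.05". It then says that "the sign/sign rank test will be used to evaluate continuous outcomes", and adds: "For non-parametric testing on unpaired continuous data, the Wilcoxon rank sum test will be used".
- **Discussion** calls the trial adequately powered for its primary endpoint and on that basis claims class II evidence.

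**The concern.** A mean change and its SD in treated people describe a before-after comparison within one arm. The trial's question is whether the change on vitamin D differs from the change on placebo. That contrast carries the sampling error of two arms, so a size that suits the first question is too small for the second. If 10 per group was derived for within-person change, the stated 80% does not apply to the primary endpoint. A true effect as large as the pilot's could then be missed about half the time, and a null result could be read as absence of effect on the strength of the claim of adequate power.

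The test named for continuous outcomes adds a smaller problem. The slash admits two tests of quite different power, and some printed sizes are ones at which neither test can be significant.

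**Working it through.** **Inputs** (Sample size section; d = mean/SD of the change)

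- IL-17 after anti-CD3: 44.5/44.3, d = 1.005, stated n = 10
- IFN-γ after PPD: 1860/1835, d = 1.014, stated n = 10
- Th1 cells: 4.3/6.3, d = 0.683, stated n = 19
- Th17 cells: 1.9/1.8, d = 1.056, stated n = 5
- Two-sided 5%, power 80%

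**1. Reproducing the plan's sizes.** For a paired t-test, power comes from the noncentral t with n−1 degrees of freedom and noncentrality d√n.

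- IL-17: 1.005 × √10 = 3.18, power 80.7% (75.2% at n=9). Size 10.
- IFN-γ after PPD: 1.014 × √10 = 3.21, power 81.3% (75.9% at n=9). Size 10.
- Th1: 0.683 × √19 = 2.98, power 80.3% (77.9% at n=18). Size 19.

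All three match. The alternatives tried do not. In the same order, a two-sample t-test gives 17, 17 and 35, and a one-sided paired t-test gives 8, 8 and 15. The normal approximation (1.96 + 0.842)²/d² gives 7.8, 7.6 and 16.8, hence 8, 8 and 17.

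Of the other four sizes, the two IL-10 entries (paired t: 2 and 3) are consistent with fewer than 5. Two do not fit: Th17 needs 10, not 5 (power at 5 is 43.7%), and IFN-γ after anti-CD3 (32.8 ± 1.2) needs 2, not 6.

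**2. Power for dose versus placebo.** The pilot gives nothing for placebo, so assume normal changes, the pilot SD in both arms and zero mean placebo change. The noncentrality is then d√(n/2). At n=10 it is 1.005 × √5 = 2.25 and 1.014 × √5 = 2.27. Rank sum power was simulated with exact critical values. The arms have 39/3 = 13 controls and 45/3 = 15 patients; after the planned drop-out, 13 × 0.8 = 10.4 and 15 × 0.7 = 10.5 remain. Each cell gives IL-17, then IFN-γ after PPD.

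| n per arm | two-sample t | rank sum |
|---|---|---|
| 10 | 56.6%, 57.3% | 51%, 52% |
| 13 | 69.1%, 69.8% | 64%, 65% |
| 15 | 75.7%, 76.4% | 72%, 73% |
| 17 | 81.1%, 81.7% | 79%, 79% |
| 18 | above 80% | 81%, 81% |

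The fall from 81% (paired t) to 57% (two-sample t), about 24 points, comes from the comparison. The further fall to 51–52%, about 5 points, comes from using ranks.

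**3. Range over assumptions the document does not give** (rank sum, 10 per arm, simulated, one change at a time):

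- placebo SD half the pilot SD: 71–72%
- placebo mean change one quarter of the pilot change, same direction: 32–33%
- heavy-tailed changes (t with 3 df, scaled to the same SD): 75–76%, rising to about 87% at 13 per arm

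None reaches 80% at 10 evaluable per arm.

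**4. Within-arm change at n=10** (normal changes). The sign test rejects at 9 or more of 10 in one direction, since 2 × 11/1024 = 0.021. With p = Φ(d), power is p⁹(10 − 9p): p = 0.842 gives 51.7% for IL-17, and p = 0.845 gives 52.5% for IFN-γ after PPD. Simulated signed-rank power is about 79% and 80%.

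**5. Very small sizes.** For the sign or exact signed-rank test the smallest two-sided p is 2 × 0.5ⁿ: 0.125 at n=4, 0.0625 at n=5 and 0.031 at n=6. For the rank sum test at 4 v 4 it is 2/70 = 0.029.

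**The case against.** The immunologic endpoints are declared exploratory and unadjusted for multiplicity, and a journal article may leave the choice between two rank tests to a fuller document. Both points are fair, and the choice between sign and signed-rank would not be a finding alone. But the article itself asserts 80% power and adequate power for the primary endpoint, and those statements do not follow from the calculation shown.

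The between-arm figures rest on an assumed placebo SD, placebo change and distribution. That stands. With heavy tails and full retention the power could exceed 80%. No assumption tried restores 80% at the 10 evaluable per group that the plan itself uses.

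Three stronger readings are tempting, and the document does not support them:

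- *That replacing a t-test with non-parametric tests destroys the power.* For within-arm change the signed-rank test loses only 1 to 2 points against the paired t-test at n=10. The sign test's 52% holds only if that option is chosen, changes are normal and exactly 10 are evaluable; it is about 66–67% at 13 and 80% at 15. Under heavy tails it is higher.
- *That the trial has zero power under its own tests.* This is true of the printed sizes of five and below, but no analysis is planned at such sizes. At n=10 both IL-10 endpoints (d of 16.9 and 6.7 in absolute value) have essentially full power even by the sign test.
- *That every printed size is a paired t-test size.* Five of seven are consistent with it, two of these only as fewer than 5. The method is inferred, since none is named.

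**Conclusion.** The point holds for the primary comparison. The sizes that fix the trial at 10 per group are within-person sizes, while the primary endpoint is a contrast with placebo. Under normal changes, equal SDs and no placebo change, power at 10 evaluable per group is about 51–52% by rank sum and 57% by two-sample t. About 18 and 17 per group respectively would be needed for 80%, more than the 13 or 15 randomized. Most of the shortfall comes from the mismatch of comparison; the rank test adds little.

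The sign-test option and the printed sizes of five or fewer are secondary. They affect the clarity and correctness of those statements, not the feasibility of an analysis at 10 per group. The trial remains usable as an exploratory study; what cannot stand is the stated 80% as a property of the placebo comparison.

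**What to change.** - **Statistical methods:** name the between-arm test of change from baseline, each dose against placebo, as the analysis of the primary endpoint. Keep any within-arm test as supportive, make it the signed-rank test, and drop the plain sign test. A plain rank test does not make the serum 25(OH)D adjustment promised in the same section, so say whether the adjusted or the unadjusted analysis is primary.
- **Sample size:** state the test assumed, and give the power at 10 evaluable per group for dose versus placebo with its assumptions (about 51–52% by rank sum for the two endpoints with d near 1, as set out above). Correct the five for Th17, which is 10 even by the paired t-test. Replace the entries below 5 with sizes the named test can support: at least 6 for a signed-rank test, at least 4 per group for a rank sum test. Recheck the 6 for IFN-γ after anti-CD3, which does not follow from its printed mean and SD.
- **Discussion:** amend the claim of adequate power to match.

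This takes a few sentences and no extra participants. The cost is a less favourable stated power.
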